#### Statistical analyses

2.3.7

The data collected will be used to answer various research questions. Hence different analyses will be conducted. First, data quality checking will be performed to ensure that discrepancies, errors, or duplicates are excluded from further analyses and overall data consistency is given. Second, data will undergo exploratory data analysis. Finally, depending on the variables available, appropriate statistical tests (e.g., linear regressions, Student's t-tests, Chi^2^-tests) will be applied to uncover differences related with rehabilitation timing after LSS surgery. Statistical analyses will be performed using IBM SPSS 28.0 (IBM Corp., Armonk, NY, USA) software.a)Subjective (ODI, SF-12) and functional performance (handgrip strength, FRT) of early and later post-operative rehabilitation intervention groups will be compared using multivariate general linear mixed model and Chi^2^-test (categorical data, specifying frequencies in percent).b)Subjective and functional performance of surgically (two groups) and conservatively treated patients with LSS and controls without spinal impairments will be compared using multivariate general linear mixed model and Chi^2^-test (categorical data, specifying frequencies in percent).c)Subjective and functional performance before and after the intervention(s) will be compared using multivariate general linear mixed model and Chi^2^-test (categorical data, specifying frequencies in percent).d)Associations of subjective and functional assessments will be tested by means of correlation analyses.

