## Abstract

**Background:**

Patients affected by lumbar spinal stenosis (LSS) suffer from a multifactorial degeneration of the lumbar spine resulting in narrowing of the neuroforamina and spinal canal, leading to various functional limitations. It remains unclear whether LSS patients after surgery would benefit from early post-operative rehabilitation, or if a delayed rehabilitation would be more advantageous. The purpose of this partially randomized patient preference trial is to evaluate the impact of post-operative rehabilitation timing as well as surgical intervention type on psychometric properties and functional outcomes in patients with LSS.

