### Study design

2.1

The present study is a partially randomized patient preference trial performed on patients from two different local hospitals. Measurements will be performed before the surgical intervention, at the time when the patient starts standardized rehabilitation, directly after rehabilitation and six, 12 and 24 months after rehabilitation (Fig. 1). For comparative purposes the standardized rehabilitation will be implemented by one local rehabilitation center with similar protocols for the early and late rehabilitation groups. Additionally, a conservatively treated group will be recruited within the rehab center responsible. The study was registered with the German Clinical Trials Register (ID: DRKS00032248). The SPIRIT reporting guidelines were used for this trial protocol [17]. The baseline data collection started in August 2023.

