#### Power analysis and sample size considerations

2.3.6

The ODI was set as our primary outcome measure. For this study, we approximated the sample size using a hypothetical approach. In order to estimate the number of cases needed, the ODI results of 46 patients with LSS (41% men) who underwent fusion surgery were used [45]. Considering the mean change from baseline of 16.1 points and the standard deviation of 17.8, a large effect (d = 0.9) can be expected. With a significance level of 5% and a power of 95%, the minimum sample size needed with this effect size is 15 patients with LSS who will undergo fusion surgery [one-sample *t*-test] (G*Power 3.1.9.2). Only 65% (30) of the patients reduced their ODI by at least ten points one year post-operatively [45]. Taking into account that approximately two-third of the patients included will reach the minimum clinically important difference and assuming a relatively high dropout rate of 20%, 30 patients with LSS would have to be initially included in each group.

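### The protocol does not fix which ODI comparison and exam decide the trial, and its aim, sample size and analysis sections point to different ones

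*Protocol article*

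**What the plan says.** All places are in the protocol article, and the point is taken on ODI alone.

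- **Aim (Abstract, repeated at the end of section 1):** the purpose is "to evaluate the impact of post-operative rehabilitation timing as well as surgical intervention type on psychometric properties and functional outcomes". Timing and surgery type stand side by side.
- **Exams (2.1):** after the pre-operative exam, patients are measured "at the time when the patient starts standardized rehabilitation, directly after rehabilitation and six, 12 and 24 months after rehabilitation". That makes five post-operative exams, and none is called primary.
- **Sample size (2.3.6):** the effect is a within-patient change: "Considering the mean change from baseline of 16.1 points and the standard deviation of 17.8, a large effect (d = 0.9) can be expected". The result is that "the minimum sample size needed with this effect size is 15 patients with LSS who will undergo fusion surgery", from a one-sample t-test. The 5% level appears only here, without a statement of one- or two-sided.
- **Analyses (2.3.7):** the section begins "The data collected will be used to answer various research questions. Hence different analyses will be conducted". It says that tests will look for differences linked to rehabilitation timing. It then lists a) early versus later rehabilitation, b) surgical (two groups), conservative and control groups, c) before versus after intervention, and d) correlations. Items a) to c) share the same model description. None is called primary, secondary or exploratory, and none names an exam.

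**The concern.** A trial's deciding contrast and time point define its question and its sample size. Here three sections that should agree on them do not: the aim has two questions, the sample size answers a third, and the analysis list carries several without ranking.

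Two things follow:

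- **A misdirected claim.** ODI is expected to fall by about 16 points after surgery whether rehabilitation is early or late. Item c) would then be significant and could be reported as the trial's ODI result, although it says nothing about timing.
- **A free choice of exam or aim.** Early and late groups may differ at one exam and not at another. With no exam named, the most favourable can be chosen after the data are seen, and 5% no longer describes the chance of a false timing claim.

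**Working it through.** **1. Reproduce the plan's figure.** Inputs from 2.3.6: mean change 16.1, SD 17.8, level 5%, power 95%.

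- d = 16.1 / 17.8 = 0.904, given as 0.9.
- One-sample t-test, exact noncentral t, one-sided 5%: n = 15 gives power 95.2% at d = 0.9. The stated 15 is reproduced.
- Two-sided 5%: n = 15 gives 89.9%, and 19 would be needed at d = 0.9.
- Inflation: 15 / 0.65 = 23.1, rounded up to 24; 24 / 0.80 = 30 per group. The stated 30 is reproduced.

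The sample size is therefore built on item c), in fusion patients only. It is not built on timing or on surgery type.

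**2. How easily c) succeeds.** After 20% dropout, 30 × 0.8 = 24 patients remain per group. With d = 0.904, a two-sided one-sample t-test has 98.9% power. A significant before-after result is close to certain if the protocol's own assumption holds, even when early and late rehabilitation are equivalent.

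**3. What the same numbers give for timing.** Assume that the SD of 17.8 also applies between groups, and take a 10-point difference for scale (the reduction that 2.3.6 uses to count responders). By normal approximation, power = Φ(10 / (17.8 × √(2/n)) − 1.96):

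- n = 30 per group: Φ(2.176 − 1.960) = 59%.
- n = 24 per group: Φ(1.946 − 1.960) = 49%.

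The stated 95% does not carry over to this contrast.

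**4. Chance of a false claim if the choice stays open.** Assumptions: each test two-sided at 5%, and equal correlation ρ between exams. The documents give neither the correlations nor any per-exam testing rule.

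| Reading | Tests | Chance of at least one false claim |
|---|---|---|
| Timing, one omnibus test | 1 | 5% |
| Timing and surgery type, one independent test each | 2 | 1 − 0.95² = 9.75% |
| Timing at 6, 12 and 24 months, ρ = 0.8 | 3 | 9.8% |
| The same, ρ = 0.5 | 3 | 12.5% |
| The same, ρ = 0 | 3 | 1 − 0.95³ = 14.3% |

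The values for ρ = 0.5 and 0.8 come from integrating over the shared normal component of three equicorrelated z-tests.

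**The case against.** **It is only a condensed article.** Testing hierarchies and level splits are commonly left to a full protocol or analysis plan, and their absence alone would be no finding. That is right. What remains is that the aim, the sample size and the analysis list are all stated here and point to different questions. A later plan could not settle this without departing from at least one of them.

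**Timing is visibly the lead question.** It is the uncertainty raised in the background, the only factor randomised (2.3.8), the structure of Figure 1, the first item in 2.3.7, and the subject of that section's sentence on what the tests look for. This stands, and it makes timing the natural choice for the deciding contrast. It does not amount to naming it, because the aim puts surgery type beside it and the sample size rests on neither.

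**Stronger readings that the documents do not support:**

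- A reader might infer that every reading inflates the error rate. One omnibus timing test would keep 5%.
- A reader might multiply all contrasts by all five exams and reach much higher rates. Section 2.3.7 describes a mixed model and no test at each exam, and the exam at rehabilitation start comes before the programme has been given. The two surgical groups in b) could also be early and late rather than the two operations.
- A reader might count all pairwise comparisons among the groups in b). That assumes patients and unimpaired controls have equal ODI, which is not a plausible null.
- A reader might count c) as a source of false positives. The effect in c) is expected to be real, so the risk is a claim about the wrong question.

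**Conclusion.** The point holds in a limited form. The protocol does not fix which ODI comparison and exam decide the trial, and its sections disagree on the comparison. The clearest risk is that a nearly certain before-after gain (98.9% power on the protocol's own figures) is presented as the trial's result.

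The second risk is selection among exams or aims. It is about 10% to 14% for three follow-up exams tested separately, 9.8% for two co-equal aims, and absent if timing is judged by one test. These figures rest on a two-sided 5% level per test, independence of the two aims' tests, separate testing at each exam and assumed correlations. They illustrate what the text leaves open and are not error rates of a stated procedure.

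**What to change.** In 2.3.7:

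- Name early versus delayed rehabilitation on ODI at one pre-specified exam, estimated from the longitudinal mixed model at two-sided 5%, as the deciding analysis.
- Label the other exams for the same contrast as supportive.
- Label b), c) and surgery type as secondary or exploratory. If surgery type is to stay a co-equal aim, apply Holm across the two contrasts (smaller p-value against 2.5%, then the other against 5%).

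When choosing the exam, note that follow-up runs from the end of rehabilitation (2.3.5). The 12-month exam is therefore not the one-year post-operative time point of the reference data in 2.3.6, and it falls later after surgery in the delayed group.

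In 2.3.6, state that the sample size was derived for before-after change in fusion patients and does not give 95% power for the timing contrast.

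**Cost:** wording in the two sections and the registry entry, fixed before outcome data are analysed. The article already provides for amendments and registry updates. No visits are added. Results on surgery type (unless kept co-equal under Holm) and at other exams can no longer be presented as confirmatory. The wording also does not repair the power for timing; it makes that limitation visible.

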Functional electrophysiological examinations (surface EMG) of muscles in LSS patients are very rare. However, these can provide concrete evidence of muscular function and coordination and thus detect dysfunction or dyscoordination. A correlational study examining gait and muscle activation characteristics could demonstrate increased paraspinal and gluteal muscle activity in patients with LSS [14]. After decompression surgery, patients showed decreased paraspinal and increased gluteal muscle activation [15]. Unfortunately, co-activity or symmetry were not examined here.

Active rehabilitation one to two months after surgery results in pain reduction and improves overall health in patients with lumbar disk degeneration [16]. However, it remains unclear whether LSS patients would benefit from early postoperative rehabilitation, or if a delayed rehabilitation would be more advantageous. In our regional setting, depending on the preference of the surgeon, both approaches are implemented.

This controlled and partially randomized patient preference trial aims to evaluate the impact of post-operative rehabilitation timing as well as surgical intervention type on psychometric properties and functional outcomes in patients with LSS. To identify predictors for intervention success or failure, patient-related outcome measures, functional tests, and surface EMG measurements will be used.

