### Study participants

2.2

The study participants are at least 18 years old. An overview of the inclusion and exclusion criteria is given in Table 1. Patients suffering from LSS will undergo surgical intervention or conservative treatment with a standardized rehabilitation program at the same rehabilitation center for three weeks (15 intervention sessions each lasting 4 to 5 h). LSS patients will be recruited and treated in two local but independent spinal surgery centers. The conservatively treated group will be enrolled at the rehab center. Patients meeting the inclusion criteria listed in Table 1 will be included consecutively in the study. Control participants will be recruited through public announcements. Furthermore, patients will be encouraged to recruit controls without any known lumbar spinal impairments of approximately the same age, sex, and activity status from their own environment.

**Table 1 tbl1:** Inclusion and exclusion criteria for the patients.

Inclusion criteria	Exclusion criteria
- Age: at least 18 years old - Voluntary participation - Signed consent - Anatomical lumbar spinal stenosis with characteristic symptoms - Present pain (NRS >3) - Agreement to be treated in the selected rehabilitation facility	- Children and adolescents - Neurodegenerative diseases - Previous spine surgery - Fractures on the lumbar spine (<2 years) - Degenerative lumbar scoliosis (>20°) - Spondylolisthesis > Meyerding 1 (3–14 mm) - ASA classification [18] >4 - Pain (NRS <3) - Orthopedic history at the lower extremities, limiting the patient's activity

For representative sampling, the study collective is self-monitored with regard to the proportion of females included, the preferred post-operative rehabilitation timing, and other parameters that may need to be balanced in periodic meetings of the participating study centers.

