#### Patient and public involvement (PPI) statement

2.3.8

Early or delayed start of the rehabilitation program will be randomized for the surgically treated patients. If patients don't want to be randomized, they can choose their preferred starting time of the post-surgical rehabilitation program. Control participants will be recruited through public announcements. Furthermore, patients will be encouraged to recruit controls without any known lumbar spinal impairments from their own environment in order to increase the chance of getting comparable control subjects in terms of sex, age, and activity level. Patients' and controls' will be asked about their experience with the assessments in order to better estimate and compare the exhibited strain and perceived exertion of the functional tests.

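### The early-versus-later comparison is defined by timing alone, so as written it mixes randomised patients with patients who chose their timing

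*Protocol article*

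**What the plan says.** The Study design section states: "The present study is a partially randomized patient preference trial performed on patients from two different local hospitals". The two allocation routes are described in the Patient and public involvement statement. First, "Early or delayed start of the rehabilitation program will be randomized for the surgically treated patients". Second, "If patients don't want to be randomized, they can choose their preferred starting time of the post-surgical rehabilitation program". Both routes feed the same two timing groups.

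The Statistical analyses section gives the general purpose of the tests, which "will be applied to uncover differences related with rehabilitation timing after LSS surgery". Item a) then applies it to ODI, SF-12, handgrip strength and the functional reach test: "early and later post-operative rehabilitation intervention groups will be compared using multivariate general linear mixed model". Items a) to d) contain no restriction to randomised patients, no separate estimate by allocation route and no term for route.

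The sample size section asks for 30 patients in each group without dividing them into randomised and choosing patients. The article gives no expected randomised share.

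**The concern.** The choice of who is compared with whom decides what a preference design can show. Among randomised patients, early and later groups differ only by chance at allocation. Among patients who choose, they may differ in anything that drives the choice. The article itself names such factors: the section on patient-reported outcome measures says that attitude, expectations and goals can affect rehabilitation results, and raises a possible hidden wish for early retirement. These could plausibly influence both the timing a patient picks and the self-reported ODI, of which the sample size section says: "The ODI was set as our primary outcome measure".

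If both kinds of patient enter one contrast, a difference between early and later groups cannot be attributed to timing with the confidence that randomisation would give. If the analysis set is left open, it could also be settled after the results are known.

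**Working it through.** **Is mixing the right reading?** The article never says that all patients are pooled, so this is an inference from three places.
- The Patient and public involvement statement fills the early and delayed groups by both routes.
- The caption of Fig. 1 uses the same name for the study's intervention groups as item a) does, so item a) compares whole groups.
- The sample size section sizes each group as a whole.

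No section points the other way.

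**The plan's own figures.** The article gives a change of 16.1 with SD 17.8, hence d = 0.9, at 5% significance and 95% power. A one-sided one-sample t-test gives n = 15 (power 0.952), as stated. Inflation: 15/0.65 = 23.1, rounded up to 24, and 24/0.8 = 30, as stated. This sizes a within-group change and not an early-versus-later difference. It is used below only for the SD and for the completers: 30 × 0.8 = 24 per group, if a group means a timing arm.

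**Illustration of bias.** Assumptions not in the article: share choosing p; a spurious early-versus-later difference c of 5 to 10 ODI points among choosers; no true effect; the same early:late split in both routes; unadjusted two-sided 5% test.

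- Bias: b = p × c. With p = 0.5, b = 2.5 to 5 points.
- SE = 17.8 × √(2/24) = 5.14.
- Type I error = 1 − [Φ(1.96 − b/5.14) − Φ(−1.96 − b/5.14)]. This gives 0.078 for b = 2.5 and 0.164 for b = 5. The noncentral t version gives 0.076 and 0.159.

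| Share choosing | Bias (points) | Type I error (noncentral t) |
|---|---|---|
| 25% | 1.25 to 2.5 | 6% to 8% |
| 50% | 2.5 to 5 | 8% to 16% |
| 75% | 3.75 to 7.5 | 11% to 30% |

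For scale, the sample size section counts ODI reductions of at least 10 points when it discusses the minimum clinically important difference.

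**Cost of a randomised-only estimate.** Power for an assumed 10-point difference, two-sided 5% t-test, SD 17.8:

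| Share randomised | Per arm | Power |
|---|---|---|
| 100% | 24 | 48% |
| 75% | 18 | 37% |
| 50% | 12 | 26% |
| 25% | 6 | 14% |

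With 12 per arm in each route, the SE within one route is 17.8 × √(2/12) = 7.27. The SE of the route-by-timing interaction is 7.27 × √2 = 10.3, so its 95% interval extends about 1.96 × 10.3 = 20 points either way.

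**The case against.** The strongest reply is that item a) is a single summary sentence. It names outcomes, groups and a model family, but no analysis population or covariates, and a fuller protocol or SAP may supply them. This stands for covariates: that baseline ODI, centre and surgery type are not listed is not an error in the article. It does not dispose of the main point. Item a) does define the contrast, and defines it by timing alone in a design whose distinguishing feature is two routes into each timing group.

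The magnitude is also fairly challenged. The share choosing, the confounding and the equal split are all assumed. The SD is for change in a fusion cohort, and a simple two-group test stands in for the mixed model. The figures show what could happen and are not an estimate.

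Four stronger readings are tempting, but the documents do not support them.
- A reader might infer that the result will be passed off as randomised. The article openly calls the trial partially randomised and nowhere describes the timing estimate as randomised evidence.
- A reader might infer that enrolment is steered by preference, because the Study participants section mentions "the preferred post-operative rehabilitation timing, and other parameters that may need to be balanced in periodic meetings of the participating study centers". That sentence concerns monitoring for representative sampling and states no mechanism.
- A reader might take "In our regional setting, depending on the preference of the surgeon, both approaches are implemented" as the trial's allocation rule. It describes existing local practice in the Background.
- A reader might infer that a recoverable preference effect is lost. Only patients who decline randomisation choose, so comparing the two routes is itself non-randomised. Separate estimates also remain possible if the route is recorded.

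**Conclusion.** The concern holds in a limited form. As written, the timing contrast in item a) combines randomised and self-selected patients and is not protected by randomisation. Randomised patients stay in the data, but their contrast is not isolated. That both routes are mixed is inferred from how the groups are formed and named; no section contradicts it.

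The size of the bias cannot be derived from the article. The 2.5 to 5 points and 8% to 16% type I error depend wholly on the assumptions listed above, and both shrink towards no bias and 5% as the randomised share approaches 100% or the confounding approaches zero. The need for change rests on the structure of the comparison and not on these figures.

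**What to change.** Amend item a) before outcomes are analysed:

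1. Estimate the early-versus-later effect in randomised patients, as randomised, and label this the randomised evidence.
2. Report the same contrast separately in patients who chose their timing, labelled observational and adjusted for pre-operative ODI, centre and surgery type.
3. Give a combined model with allocation route and route-by-timing terms as a secondary analysis. Note that a route main effect alone does not remove confounding among choosers: it absorbs an overall difference between the two cohorts, but the timing estimate still averages the randomised and the self-selected contrasts.
4. State the expected randomised share, and record the allocation route for each surgical patient.

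This changes wording and needs no new measurements beyond the route. The real cost is precision. If half are randomised, the randomised-only estimate has about 26% power for 10 points, and the interaction is too imprecise to show that the two routes agree. If few patients accept randomisation, the report must say that the timing conclusion is largely observational.

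### Item c) of the statistical analyses names a Chi-square test for categorical before-after data from the same patients, which ignores the pairing

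*Protocol article*

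**What the plan says.** The section Statistical analyses (2.3.7) lists four analyses. Items a) and b) compare separate groups of people: early against later rehabilitation, and surgical, conservative and control groups. Item c) compares time points: "Subjective and functional performance before and after the intervention(s) will be compared using multivariate general linear mixed model and Chi^2^-test". All three items use the same parenthesis to say where the second test applies: "Chi^2^-test (categorical data, specifying frequencies in percent".

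The section Study design (2.1) shows that each patient is measured repeatedly: "Measurements will be performed before the surgical intervention, at the time when the patient starts standardized rehabilitation, directly after rehabilitation", and again at six, 12 and 24 months.

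The opening of 2.3.7 is looser: "appropriate statistical tests (e.g., linear regressions, Student's t-tests, Chi^2^-tests) will be applied to uncover differences related with rehabilitation timing". That sentence is about rehabilitation timing, and Chi-square is the only categorical test it lists. No paired or repeated-measures method for categorical data is named anywhere in the article.

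**The concern.** A Chi-square test on a time-by-category table treats the before and after values as two independent samples. In item c) each patient contributes to both rows. The variance of the difference between two paired proportions contains a covariance term that the test leaves out. When patients tend to keep their category over time, the covariance is positive, the test overstates the variance, and its true error rate falls below the nominal 5%. Real changes are then harder to detect.

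There is a second way to lay out the same data, with the before category in rows and the after category in columns. A Chi-square test on that table asks whether the two visits are associated. They almost always are, even when nothing has changed, so a significant result could be misread as change.

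The protocol names the test for this comparison, so this is a stated choice and not a detail left to another document.

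**Working it through.** **1. The plan's own figure, and where 24 pairs comes from.** The article gives no sample size for a categorical comparison. Its only figure is for the mean change in the Oswestry Disability Index (ODI): "Considering the mean change from baseline of 16.1 points and the standard deviation of 17.8, a large effect (d = 0.9) can be expected", then "With a significance level of 5% and a power of 95"%, and "the minimum sample size needed with this effect size is 15 patients with LSS who will undergo fusion surgery".
- 16.1 / 17.8 = 0.904.
- A one-sample t-test with d = 0.9, one-sided 5% and n = 15 has power 0.952, so 15 reproduces as a one-sided calculation.
- 15 / 0.65 = 23.1, rounded up to 24. Then 24 / 0.8 = 30, which matches "assuming a relatively high dropout rate of 20%, 30 patients with LSS would have to be initially included in each group".
- After 20% dropout, 30 × 0.8 = 24 patients per group. This is the number of pairs used below.

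**2. Assumptions not in the documents.** Binary outcome; two visits; 50% at both visits under no change, 50% to 75% under change; paired values from a bivariate normal cut at those proportions, with latent correlation 0, 0.3, 0.5 or 0.7. Two-sided 5%.

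**3. Formulas.** Let b and c be the counts of patients who change in each direction, n the number of pairs, and φ the correlation of the two binary values.
- True variance of the difference: [p₁(1−p₁) + p₂(1−p₂) − 2φ√(p₁(1−p₁)p₂(1−p₂))] / n. The unpaired Chi-square drops the φ term.
- McNemar statistic: (b − c)² / (b + c), on 1 degree of freedom.
- Large-sample true size of the unpaired test at equal proportions: 2[1 − Φ(1.96 / √(1 − φ))].

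Worked case, latent correlation 0.5, no change: P(positive at both visits) = 1/4 + arcsin(0.5)/(2π) = 1/3, so φ = (1/3 − 1/4)/(1/4) = 1/3. Size = 2[1 − Φ(1.96/0.816)] = 2[1 − Φ(2.40)] = 0.016. The small-sample value at 24 pairs is 2.1%.

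**4. Results at 24 pairs** (summing multinomial probabilities over all possible tables; simulation agrees to about a point).

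| Latent correlation | Chi-square size | Power: Chi-square | Power: McNemar mid-p | Power: McNemar asymptotic | Power: McNemar exact |
|---|---|---|---|---|---|
| 0 | 5.9% | 45% | 40% | 40% | 31% |
| 0.3 | 3.6% | 44% | 46% | 46% | 36% |
| 0.5 | 2.1% | 44% | 52% | 53% | 41% |
| 0.7 | 0.8% | 43% | 61% | 65% | 48% |

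**5. Sensitivity on another scale.** With φ fixed directly and a change from 50% to 25%, 30 pairs give 52% (Chi-square) against 64% (asymptotic McNemar) at φ = 0.3, and 52% against 84% at φ = 0.5. With 48 pairs (two groups of 24 pooled), φ = 0.3 gives 76% against 86%. A negative φ would reverse the direction: the large-sample size is 7.4% at φ = −0.2.

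**6. The other layout.** A Chi-square test on the before-by-after cross-table at 24 pairs, with no change at all, rejects about 40% of the time at latent correlation 0.5 and 72% at 0.7.

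**The case against.** **No named outcome depends on this test.** The primary outcomes (ODI, walking distance) and secondary outcomes (handgrip strength, functional reach) are scored or continuous. Item c) gives these a mixed model, which can handle pairing. This stands, and it sets the severity. A reader might infer that the trial's main before-after conclusions are unsound; the documents do not support that.

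**No categorical before-after endpoint is named.** The nearest candidate is the WHO grade of pain medication in 2.3.1, which is recorded but not listed as an outcome. The ten-point ODI threshold in the sample-size section is itself a change score, so it has no before value. This also stands: the size of the problem rests on assumed inputs. Item c) nevertheless provides for categorical data explicitly.

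**A conservative test makes no false claims.** This is true of the time-by-category layout under positive correlation. It is not true of the cross-table layout, where the result does not address change.

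**The wording is condensed and could loosely cover McNemar's chi-square.** This is possible. But the wording is identical in items a) and b), where it can only mean the ordinary test, so the plain reading is the unpaired one.

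**Switching to a paired test is not free of cost.** This stands in part. Exact McNemar is itself conservative: at latent correlation 0.5 it has 41% power against 44% for Chi-square. It would be wrong to infer that any paired test improves on Chi-square in every setting.

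**Conclusion.** The concern holds in limited form. As written, item c) applies a test for independent samples to paired categorical data. Under positive within-patient correlation its true error rate is below 5%, and it loses power against mid-p McNemar. In the assumed setting the difference is about 2 points at latent correlation 0.3, 8 points (52 − 44) at 0.5 and 18 points (61 − 43) at 0.7. At zero correlation Chi-square is ahead by about 5 points (45 − 40). Positive correlation is the expected case, but its size, the proportions and the number of pairs in the analysis are assumptions; item c) does not say whether the comparison is run within one group.

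Severity is minor to moderate. The stated analysis should be corrected, but no named primary or secondary outcome is affected.

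**What to change.** In item c) of 2.3.7, replace the Chi-square test as follows:
- binary data at two visits: McNemar's test, mid-p or asymptotic, and not the exact version;
- binary data at more than two visits: Cochran's Q, or a logistic mixed model or GEE with patient as the cluster;
- graded data such as the WHO medication grade: a marginal-homogeneity test, or an ordinal mixed model or GEE. McNemar and Cochran's Q would force a dichotomy that the plan does not contain.

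Keep the Chi-square test in items a) and b) for comparisons of independent groups at a single visit.

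The cost is one sentence, with no new data and no change to the sample size. The only statistical downside is slightly lower power if the within-patient correlation turns out to be near zero.
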